3.2 EXPERIMENTAL DESIGN

CLINICAL CONTROLLED TRIAL _X_

COHORT STUDY ___

CASE-CONTROL STUDY ___

CROSS-SECTIONAL STUDY ___

3.3. SOURCE OF VARIATION

RANDOMISED _X_ DESCRIPTIVE ___

LONGITUDINAL _X_ SECTIONAL ___

PROSPECTIVE _X_ RETROSPECTIVE ___

**4. METHODOLOGY**

4.1. PLACE AND TIME EXPERIMENT

The study will conducted in the obstetrics department of the “Isidro Espinosa de los Reyes” National Institute of Perinatology from November 2008 to September 2011. A prospective, randomised, double-blind, controlled clinical trial (RCT) will conducted to compare the efficacy and clinical safety of the induction of labour using the combination of isosorbide dinitrate-oxytocin (experimental arm, X=1) compared to misoprostol-oxytocin (standard arm, X=0). The drug´s characteristics that facilitates cervical ripening of women with intrauterine foetal death after 20 weeks of gestation and lack of uterine activity is clearly detailed in the following description and the accompanying tables and three figures highlight the site and mode of action of the drug as well as the recruitment and assignment of patients to each of the experimental groups.

4.2. UNIVERSE, EXPERIMENTAL UNITS, METHODS OF SAMPLING, AND SAMPLE SIZE.

4.2.1 UNIVERSE, AND EXPERIMENTAL UNITS

All pregnant women who come to National Institute of Perinatology.

All women with intrauterine foetal death after 20 weeks of gestation and lack of uterine activity, and to meet the criteria for inclusion.

4.3 DRUG DEVELOPMENT AND MANAGEMENT THERAPY

An isosorbide dinitrate- or misoprostol-based solution will prepared according to the previously published specifications.9 A base solution of isosorbide dinitrate and misoprostol will prepared to obtain a concentration of 20 mcg/mL in 10% lactose solution. Serial dilutions will performed using known concentrations in mobile phase buffer solution (150 g ammonium acetate and 11.5 mL glacial acetic acid to 1 L water), methanol and water in a proportion of 350:100:550, respectively. The concentration of both drugs will determined using a UV spectrophotometer (Spectrophotometer UV, Beckman DU 65, CA, USA) reading at E 220 nm and a reference filter of E 278 nm. The mean absorbance for each set of standards, controls and samples will calculated by a standard plot curve. Computer-based curve-fitting statistical software will employed. Peak absorption and area under the curve will taken into account to determine stability of the pharmacological integration. Known samples of isosorbide dinitrate and misoprostol will add to 100% glycerin to prepare the gel solution. The reagents will have final concentrations of either 80 mg of isosorbide dinitrate in 1.5 ml of gel solution or 100 mcg of misoprostol in the same presentation. Both solutions will packed in syringes that has the same appearance for the purpose of keeping the physician, patient and researcher blinded. The pharmacist will be the only participant who knew the contents of the syringes. Four syringes will placed in an opaque and sealed envelope consecutively numbered with a unique study number. The envelopes will open by the physician who applied the contents of the syringe, repeating the administration every 3 hours according to the prior selection and random allocation of patients. The entire "stock" of reagents remain stable for a period of 20 days and will maintain at room temperature (18-25° C) before using.

Opaque envelopes contained each microvial, and a consecutive number will assigned to each one and then sealed. These will randomly opened by the physician who applied the content of the microvial to the endocervix. Informed written consent will obtained and the study will be submitted for approval by the Ethics Committee of the National Institute of Perinatology.

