2.5. OBJECTIVE AND HYPOTHESIS

2.5.1. OBJECTIVE OF EXPERIMENT

The main objective of our study is to compare the efficacy and adverse effects of the intravaginal administration of isosorbide dinitrate in gel form followed by a high dose of oxytocin for the induction of labour after late foetal death with a commonly utilised combined regimen, misoprostol-oxytocin. Also, we will establish adverse events such as blood pressure, respiratory rate, and temperature, as well as nausea, headache, vomiting, diarrhea, fever, chills, abdominal pain and vaginal bleeding in women treated with misoprostol or isosorbide dinitrate.

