4.5. DATA COLLECTION

Data of the treatment will discarded, and only the study number will used to code the patient’s measurements. The type of treatment remained unknown to the participating women, and at the end of study period the results will analysed. All participants were given a vaginal exam by the same person, who was blinded to the treatment allocation. The medications were administered in the posterior fornix, and cervical activity was evaluated at baseline and every 3 hours to monitor any change based on the Bishop score.

If the cervical conditions did not change after the treatment application, participants will receive a new dose, without exceeding 4 doses, to facilitate cervical ripening. Once a Bishop score of over 7 will reached, oxytocin will infused in a balanced electrolyte solution beginning with an infusion rate of 2 mIU/min and doubling the dose every 15 minutes. The labour induction time from the first application of medication to the expulsion of the foetus will determined with a digital stopwatch. Each woman's vital signs will verified to determine that she is in stable condition and demonstrated haemodynamic stability as a requirement for the application of a new dose. During this time, the data and medical information will collected on paper and will later entered into a computational database. The participants will remain at rest during the evaluation of adverse effects, such as headache, abdominal pain, pelvic pain, lower back pain, nausea, dizziness, and vomiting. The lack of cervical activity after 4 doses of medication will considered treatment failure.

4.6. PILOT STUDY.

The purpose of conducting the pilot study will be examine the feasibility of an clinical approach study. Our pilot study can be used to evaluate the feasibility of recruitment, randomization, retention of patients and assessment procedures of the novel intervention. Ten women with ultrasonographic diagnosis of fetal death above 20 weeks gestation will be randomly selected to receive the pre-induction treatment based isosorbide dinitrate gel solution or misoprostol gel solution. The time interval between the application of pretreatment, the optimal relaxation of the cervix and conduction of labor will be determined in women in each experimental group. Also, clinical data obtained from these patients will serve to estimate the required sample size. Patients will have access to the best proven therapeutic method identiﬁed by the study.

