**6. SCHEDULE OF ACTIVITIES**

PROTOCOL REGISTRATION: 212250-29021

TITLE OF PROYECT: Intravaginal application of isosorbide dinitrate gel solution to favor cervical ripening prior to induction of labour in women with late intrauterine death.

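### Section 4.3 gives two conflicting dispensing instructions, and the second changes the application site and, read literally, how the treatment is chosen

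*Protocol*

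**What the plan says.** Section 4.3 describes packaging and dispensing twice, in adjacent paragraphs.

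The first paragraph says that both gels go into syringes of the same appearance and that only the pharmacist knows the contents. It continues: "Four syringes will placed in an opaque and sealed envelope consecutively numbered with a unique study number". The physician opens the envelope and gives the contents, "repeating the administration every 3 hours according to the prior selection and random allocation of patients".

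The second paragraph says: "Opaque envelopes contained each microvial, and a consecutive number will assigned to each one and then sealed". It then says: "These will randomly opened by the physician who applied the content of the microvial to the endocervix". A sentence on consent and ethics approval follows.

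Three other places bear on the site. The objective in section 2.5.1 speaks of "intravaginal administration of isosorbide dinitrate in gel form". The project title repeated in section 6 begins "Intravaginal application of isosorbide dinitrate gel solution to favor cervical ripening". Section 4.5 states: "The medications were administered in the posterior fornix".

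Section 4.5 also caps treatment at four doses, has the Bishop score assessed at baseline and every 3 hours, and codes measurements by study number alone once treatment data are set aside.

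**The concern.** The two paragraphs cannot both be followed. They name different containers, different ways of choosing the envelope and, once section 4.5 is read alongside, different application sites.

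Two things are at stake. The first is the intervention itself. The Bishop score decides whether a woman gets another dose and when oxytocin starts, so whether the gel goes into the vaginal fornix or the endocervix is a core part of the treatment under test. The second is allocation. The trial is described as randomised and double-blind, which requires the arm to be fixed by a sequence made beforehand. An instruction that the treating physician opens envelopes at random describes something else.

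**Working it through.** No arithmetic settles this. The planned size in section 4.7, at least 30 women per group, does not depend on how the drug is packed. The check is to set the texts side by side.

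| Feature | 4.3, first paragraph | 4.3, second paragraph | Elsewhere in the protocol |
| --- | --- | --- | --- |
| Container | Syringe | Microvial | Microvials are not mentioned again |
| Units per envelope | Four | No count given; one is the natural reading | Cap of four doses (4.5) |
| Number on the envelope | Study number | A consecutive number, not said to be the study number | Measurements coded by study number (4.5) |
| Choice of envelope | Prior random allocation | Opened at random by the physician | Randomised, double-blind (4.1) |
| Site | Not stated | Endocervix | Posterior fornix (4.5); intravaginal (2.5.1 and the title) |

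**Site.** This conflict does not depend on how the allocation wording is read. The endocervix is named as the place of application only in the second paragraph. The title, the objective and section 4.5 all give a vaginal route.

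**Choice of envelope.** The first paragraph ties dosing to an allocation already made. The second, taken literally, makes the physician's pick the act that decides what is given. The wording may only be a clumsy way of saying that envelopes are opened as randomised, but it does not say so.

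**One drug per course.** Neither paragraph says outright that all of a woman's doses contain the same drug. The first implies it, since repeat doses follow the allocation of patients. The second is silent.

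**Link to the arm.** Under the first paragraph the envelope carries the study number, which is also the code for the data. The second mentions only a consecutive number. The two series may be the same; the text leaves this open.

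**Which paragraph governs.** The protocol does not say, and it does not confine the second paragraph to the pilot study. Both paragraphs are complete, so nothing lost in extraction explains the conflict.

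**The case against.** The best defence is that the second paragraph is leftover text. Section 4.3 cites an earlier first-trimester trial for the preparation of the solutions, and the reference list describes that trial as intracervical. Everything else in the protocol fits the syringe rule: four syringes match the cap of four doses, the 3-hourly interval matches the 3-hourly examination, the blinding is described only for syringes, and the route is vaginal throughout. This largely stands. A reader might infer that staff could not tell which rule to follow; the documents do not support that, because a careful reader would settle on the syringes.

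A second defence is that opaque, sealed envelopes hide their contents, so a physician picking one would not know the drug. This also stands: no loss of concealment and no bias are shown. It does not restore the prior allocation, because a pick made at the bedside is not a sequence fixed in advance.

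A third is that the assignment figure is not shown and may be clear on allocation. That is possible, but a figure would not remove a written instruction that names another container and another site.

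So the defence explains how the conflict may have arisen and limits its consequences. It does not remove two operative sentences that contradict the rest of the plan.

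**Conclusion.** Section 4.3 contradicts itself on container and choice of envelope, and its second paragraph contradicts sections 2.5.1 and 4.5 and the title on the application site. The site conflict is the firmest part. The replacement of the prior allocation follows only if the second paragraph is read literally.

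Three stronger readings are tempting and are not supported.

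- A reader might infer that women would receive both drugs. If every dose were a fresh draw with equal chances for the two drugs, the probability of a mixed course of four doses would be 1 − 2 × 0.5⁴ = 87.5%. The protocol states no such draw, no stock size and no distribution of doses, so the figure describes an assumption and not this trial.
- A reader might infer that vial numbers could not be traced to an arm. The two number series may be one, and the pharmacist knows the syringe contents.
- A reader might measure the problem by counting envelopes. One vial per envelope is a natural reading and not a stated count, and such a count says nothing about the estimate, its error rate or its power.

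No numerical effect on the results can be derived. The defect lies in the instructions, and it deserves correction because it touches the intervention and the allocation and is nearly free to cure.

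**What to change.** Delete the two microvial sentences in section 4.3 and keep the consent and ethics sentence that follows them. State one rule in their place:

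- one sealed envelope per woman, holding four syringes of the same drug;
- the envelope numbered with her study number, and envelopes opened in consecutive order;
- all doses given into the posterior fornix;
- the pharmacist holds the list of study number against drug.

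The cost is a text edit and a list. Drug preparation and sample size do not change. Syringes will be wasted when a woman needs fewer than four doses. Supply also has to be planned around the statement that the stock will "remain stable for a period of 20 days". That statement concerns the reagent stock before use. The protocol does not say whether it also limits filled syringes, so the revised text should. If it does, an expired envelope should be remade under the same number with the same drug.

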4.3.1. ELIGIBILITY

Genders Eligible for Study: Female

Accepts Healthy Volunteers: No

CRITERIA

Inclusion Criteria:

- Closed cervix without evidence of cervical dilation or baseline uterine activity.
- A Bishop score of <5, having intact membranes.
- Gestation greater than or equal to 20 weeks established by the date of menstruation or by foetometry and ultrasound-confirmed late IUFD.

Exclusion Criteria:

- Multiple pregnancies.
- IUFD after late foeticide or the management of specific medical conditions associated with an increase in the risk of IUFD.
- Patients with a history of hypertension.
- Women with a history of unexplained antepartum haemorrhage, pelvic dystocia or any another counterindications where medications were used.

4.4. CHECKLIST (VARS)

**Patiens:**

Name

Age (years)

Gestational age (weeks)

Previous deliveries

Term deliveries

Preterm labour

Prior abortions

Uterine size (mm)

Long 1

Long 2

Transverse

**Haemodynamic stability:**

Heart rate (bpm)

Respiratory frequency (xminutes)

Core temperature (°C)

Systolic blood pressure (mmHg)

Diastolic blood pressure (mmHg)

**Adverse effects:**

Headache

Abdominal pain

Pelvic pain

Lower back pain

Nausea

Dizziness

Vomiting

**Main outcome measures:**

The main result of the study will the success rate of foetal expulsion within 15 hours, while the average administration induction interval defined the secondary result.

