2.5.2. HYPOTHESIS OF EXPERIMENT

It is expected that the 97% probability of achieving successful cervical ripening (Bishop score of over 7) with 80 mg of isosorbide dinitrate gel solution at 12 hours and a 67% chance of achieving successful cervical ripening with 100 mcg of misoprostol (power of 80%, α-value of 0.05, and β-value of 0.2) with 25% of all women whose will fail to induce labour. The main adverse effect associated with the administration of isosorbide dinitrate gel solution will be the headache and women treated with misoprostol will report preferably pelvic pain.

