4.7. STATISTICAL ANALYSIS.

Sample size calculations (Figure 3) will be based on a 97% probability of achieving successful than women undergoing pre-induction therapy with isosorbide dinitrate may reach a score> 7 on the scale of Bishop at 12 hours, and 67% chance for the group of women undergoing pre-treatment with misoprostol (α = 0.05, β = 0.2). Based on these assumptions, at least 30 women will be required for each treatment group. We believe this difference based on the results observed in a preliminary way. Values ​​are presented as mean ± SD. Both IDN and MIS will be evaluated to discern the clinical efficacy using the log rank test and Kaplan-Meier. Hemodynamic data obtained from each experimental group will be analyzed by the Student t test for independent samples. The drug safety will be evaluated based on the data of adverse effects by bivariate analysis (relative risks with 95% confidence interval). The differences in signs and symptoms between groups will be determined by chi-square. P <0.05 will be considered statistically significant. All statistical analyzes will be performed using SPSS for Windows (version 10.0, SPSS Inc., Chicago, USA).

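### The 80% power and 30 per group are justified for Bishop score above 7 at 12 hours, but the declared main result is foetal expulsion within 15 hours, for which no rates or power are stated

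*Protocol*

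**What the plan says.** Section 4.4, under main outcome measures, fixes the main result: "The main result of the study will the success rate of foetal expulsion within 15 hours". The secondary result there is the average interval from administration to induction. The Bishop score does not appear in that list.

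The sample size in section 4.7 rests on a different event at a different time: "Sample size calculations (Figure 3) will be based on a 97% probability of achieving successful" ripening, meaning that women given "isosorbide dinitrate may reach a score> 7 on the scale of Bishop at 12 hours". The misoprostol figure is 67%, and the conclusion is that "at least 30 women will be required for each treatment group". Section 2.5.2 repeats the Bishop-based contrast as the hypothesis, with "power of 80%, α-value of 0.05, and β-value of 0.2", and adds the clause "with 25% of all women whose will fail to induce labour".

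Section 4.5 links the two events. Cervical status is examined every 3 hours, up to four doses are allowed, oxytocin begins once the score passes 7, and induction time runs from first application to expulsion. Section 4.7 assigns efficacy to the log-rank test and Kaplan-Meier, without saying which time is analysed.

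**The concern.** The declared main outcome and the endpoint behind the hypothesis and sample size are different, so the stated power does not belong to the result the trial names as its main one. The two endpoints are not interchangeable. Ripening is a step before oxytocin, and a woman first found ripe at the 12-hour examination has 3 hours left to count as an expulsion success (taking the 15 hours from first application, as section 4.5 does for induction time). She can succeed on one endpoint and fail on the other.

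Two things are at stake. A null result on expulsion would be hard to read, because nobody has said what difference the trial could detect on it. And with the hypothesis on one endpoint and the main result on another, a reader of the final report cannot tell which one was meant to decide the question.

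**Working it through.** **Inputs.** From sections 2.5.2 and 4.7: p1 = 0.97, p2 = 0.67, alpha 0.05, power 0.80, 30 per group. Sidedness is not stated; two-sided is assumed. Expulsion rates: none given.

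**Step 1: reproduce the 30 per group for the Bishop endpoint.**
- Pooled formula, with mean rate 0.82: n = [1.960·√(2·0.82·0.18) + 0.842·√(0.97·0.03 + 0.67·0.33)]² / 0.30² = (1.065 + 0.421)² / 0.09 = 24.5, so 25.
- With continuity correction: (n/4)·[1 + √(1 + 4/(n·0.30))]² with n = 24.5 gives 30.8, so 31.
- Unpooled formula: (1.960 + 0.842)²·(0.0291 + 0.2211)/0.09 = 7.849·0.2502/0.09 = 21.8, so 22. Inflated for 25%: 22/0.75 = 29.3, so 30.

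The stated size is therefore reasonable for ripening at 12 hours. Exact power at 30 per group for 97% against 67% is 83% (Fisher) or 93% (Pearson).

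**Step 2: what the same 30 per group gives for expulsion.** Assume a fraction q of ripened women in each arm expel by 15 hours, and that unripened women do not. The rates are then 0.97q and 0.67q. Exact power comes from summing the binomial probabilities of all outcome pairs (0 to 30 in each arm) that reach two-sided p < 0.05.

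| q (assumed, equal in both arms) | Rates | Fisher | Pearson |
|---|---|---|---|
| 1.00 | 97.0% vs 67.0% | 83% | 93% |
| 0.95 | 92.2% vs 63.7% | 69% | 79% |
| 0.90 | 87.3% vs 60.3% | 58% | 68% |
| 0.75 | 72.8% vs 50.3% | 33% | 43% |

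A loss of about 5% between ripening and expulsion in each arm is enough to take power below 80% on either test.

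**Step 3: can the 25% in section 2.5.2 settle the rates?** It has at least three readings.
- An inflation allowance: 22/0.75 rounds up to 30. It then says nothing about expulsion.
- An overall failure rate. The Bishop rates imply an average failure of (3% + 33%)/2 = 18%, so 25% would be a different event. Keeping the 30-point gap gives 90% vs 60%, power 71%/80% (Fisher/Pearson). Scaling both rates by 0.75/0.82 gives 88.7% vs 61.3%, power 61%/71%.
- Failure after ripening, equal in both arms: the last row of the table, 33%/43%.

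**Step 4: the planned test.** Under a log-rank test with proportional hazards (assumed), simulated power at 30 per group is about 81% for 88.7% vs 61.3% when times are censored at 15 hours, 86% to 93% for 90% vs 60%, and 46% to 64% for 72.8% vs 50.3%, where each range depends on whether follow-up stops at 15 hours or runs to expulsion. A formula check of the last case: hazard ratio ln(0.2725)/ln(0.4975) = 1.86 and expected events 30·(0.7275 + 0.5025) = 36.9, so √(36.9/4)·ln 1.86 − 1.96 ≈ −0.07, a power of about 47%.

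**The case against.** The strongest reply is that nothing here shows the trial to be too small. A reader might infer from the mismatch, and from the 25%, that expulsion is underpowered on the protocol's own figures. The documents do not support that. They contain no expulsion figures, the 25% is ambiguous, and every low-power value above needs an added assumption about conversion. Conversion could also differ between arms in either direction. The log-rank test that section 4.7 plans reaches 80% in some scenarios where a two-proportion test does not. All of this stands, and it limits what can be said about size.

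A reader might also infer that the protocol has two competing primary endpoints. It does not: section 4.4 names one main result and one secondary, and the Bishop endpoint is neither.

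It can be added that section 4.7 says at least 30, and that section 4.6 expects pilot data to inform the sample size. But section 4.6 does not say for which endpoint, and section 4.7 already bases its difference on preliminary results for the Bishop score. Figure 3 is not shown, but the text of section 4.7 states the basis of the calculation.

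Finally, expulsion is a defensible main result: the objective in section 2.5.1 is efficacy of the drug-oxytocin regimens for inducing labour. That argues against treating ripening as the obviously right primary. It does not remove the mismatch.

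**Conclusion.** The point holds as a contradiction within the protocol. The 97% against 67%, the 80% power and the 30 per group belong to a Bishop score above 7 at 12 hours. The declared main result, expulsion within 15 hours, has no assumed rate in either arm and no stated power.

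How much power is lost, if any, cannot be read from the document. With a two-proportion test and equal conversion, power ranges from 83%/93% (Fisher/Pearson) with no loss after ripening to 33%/43% with a 25% loss. The planned log-rank test would give different values. A shortfall is plausible but not established. The mismatch itself needs no assumption and should be corrected, because the protocol fixes the main result, the hypothesis and the sample size, and these do not agree.

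**What to change.** Use one primary endpoint in sections 2.5.2, 4.4 and 4.7. Either route resolves the contradiction.

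- **(a) Bishop score above 7 at 12 hours as the main result**, with expulsion within 15 hours as a secondary result. The existing rates, power and 30 per group then apply as written. The cost is that the main result becomes an intermediate step and sits less well with the objective in section 2.5.1.
- **(b) Expulsion within 15 hours stays the main result**, which fits section 2.5.1. The protocol then states assumed expulsion rates per arm and where they come from, says what the 25% in section 2.5.2 means, and replaces the 80% claim with the power that 30 per group gives for expulsion under the planned test.

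Both are changes of wording and need no extra women. The downside of (b) is that the stated power may be less favourable. If the sponsor then wants 80% for expulsion, more women may be needed: by the pooled formula of Step 1, uncorrected, 33, 41 or 73 per group when 95%, 90% or 75% of ripened women in each arm expel in time. These figures are illustrations under equal conversion, not values to insert in the protocol.

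### The secondary result is a plain average of an interval that is not fixed to one end event and that some women may never complete

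*Protocol*

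**What the plan says.** Under Main outcome measures (section 4.4), the primary result is "the success rate of foetal expulsion within 15 hours". For the secondary outcome, "the average administration induction interval defined the secondary result". No start or end event is given for that interval.

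Section 4.5 describes a timed quantity: "The labour induction time from the first application of medication to the expulsion of the foetus will determined with a digital stopwatch". It also separates induction from expulsion, since "Once a Bishop score of over 7 will reached, oxytocin will infused". Dosing is repeated at the 3-hourly assessments: "participants will receive a new dose, without exceeding 4 doses". On non-response it says only that "The lack of cervical activity after 4 doses of medication will considered treatment failure". It does not say what interval, if any, such a woman contributes.

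Section 4.7 says in general terms that values are "presented as mean ± SD". It assigns log-rank and Kaplan-Meier methods to clinical efficacy without naming the event, the time origin or the censoring rule.

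**The concern.** There are two linked problems.

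First, an interval from administration to induction and an interval from first application to expulsion end at different events, because oxytocin comes between them. The protocol does not say which is the secondary outcome.

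Second, an average needs a number for every woman. Under section 4.5, a woman who never passes Bishop 7 has no oxytocin start. Section 2.1 links failed induction with an unripe cervix to caesarean birth, and a woman delivered that way has no expulsion time. If the average is taken over the times that exist, it conditions on a response that occurs after randomisation and that treatment is expected to change. The arm with more failures loses more of its slow women and looks faster than it is. On the planned rates that arm is misoprostol, so the bias would run against isosorbide dinitrate.

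**Working it through.** **Inputs from the protocol.** Section 2.5.2 assumes a "97% probability of achieving successful cervical ripening (Bishop score of over 7) with 80 mg of isosorbide dinitrate gel solution at 12 hours", against 67% for misoprostol. Section 4.7 repeats these rates with α = 0.05 and β = 0.2, and asks for at least 30 women per arm. The 12-hour point matches four doses at 3-hour spacing.

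**The plan's own figure.** Two-sided test of two proportions, with mean proportion 0.82:
- n = [1.96·√(2·0.82·0.18) + 0.842·√(0.97·0.03 + 0.67·0.33)]² / 0.30² = 24.5, so 25 per arm.
- With continuity correction: (24.5/4)·[1 + √(1 + 4/(24.5·0.30))]² = 30.8, so 31 per arm.

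The stated 30 is reproduced closely, so the two rates are a fair basis for what follows.

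**Women without a ripening time at 12 hours.**
- Isosorbide dinitrate: 30 × (1 − 0.97) = 0.9.
- Misoprostol: 30 × (1 − 0.67) = 9.9.

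These counts need no distributional assumption. They apply only if the interval ends at ripening or at oxytocin start.

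**Effect on a mean of available times (illustration).** The protocol gives no distribution of times. I assume Weibull times to ripening, S(t) = exp[−(t/b)^k], with b = 12/(−ln(1 − p))^(1/k), so that each arm meets its planned rate p at 12 hours. The shape k runs from 1 (constant hazard) to 3. The illustration treats time as continuous and ignores the 3-hourly assessment grid.
- Restricted mean to H hours, all women: R(H) = ∫₀ᴴ S(t) dt.
- Mean among women with the event by H: [R(H) − H·S(H)] / [1 − S(H)].

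For k = 1 the hazards are −ln(0.03)/12 = 0.292 and −ln(0.33)/12 = 0.0924 per hour. At H = 12:
- R = 0.97/0.292 = 3.32 h and 0.67/0.0924 = 7.25 h.
- Responder means = (3.32 − 12·0.03)/0.97 = 3.05 h and (7.25 − 12·0.33)/0.67 = 4.91 h.

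Each pair below is isosorbide dinitrate, misoprostol. The share hidden is 1 − (responder difference / restricted mean difference).

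| Horizon | Shape | Responder means (h) | Difference | Restricted means, all women (h) | Difference | Share hidden |
|---|---|---|---|---|---|---|
| 12 h | 1 | 3.05, 4.91 | 1.86 | 3.32, 7.25 | 3.93 | 53% |
| 12 h | 3 | 6.87, 8.27 | 1.40 | 7.02, 9.50 | 2.48 | 43% |
| 15 h | 1 | 3.23, 5.82 | 2.59 | 3.38, 8.12 | 4.74 | 45% |
| 15 h | 3 | 7.04, 9.51 | 2.47 | 7.05, 10.14 | 3.09 | 20% |

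The 15-hour rows extrapolate the curve beyond the only time point for which the protocol gives a rate, so they depend more heavily on the shape. The direction is the same in every row.

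**Expulsion interval.** The protocol gives no expulsion rate by arm and does not say how many treatment failures later expel. No corresponding count or loss can be computed.

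**The case against.** The strongest reply is that nothing in the protocol restricts the interval to responders. That is correct. Exclusion of failures is an inference from the word average and from the lack of any value for these women; it is not a stated rule.

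Second, Kaplan-Meier and log-rank are already planned and can keep women without the event in the analysis. This also stands, and it makes the remedy cheap. But section 4.7 attaches those methods to efficacy in general, and they do not replace the average named in section 4.4.

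Third, the mean and SD line is a general reporting convention and not a rule for this outcome. Agreed; the point rests on section 4.4 alone.

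Fourth, the two sections may describe one quantity in loose wording. That is possible, but a reader cannot tell, and oxytocin start and expulsion are distinct events in section 4.5.

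Fifth, censoring rules are often left to the SAP, so their absence is not the fault raised here. The fault is that the protocol itself fixes an unsuitable summary and leaves its end event unclear.

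Two stronger readings should be resisted. A reader might apply the 3% and 33% non-response to the expulsion interval. Those rates concern ripening, and a woman who fails to ripen by 12 hours may still expel and so have a time. A reader might also set the 12-hour responder difference (1.86 h) against the 15-hour restricted mean difference (4.74 h) and conclude that about 60% is hidden. That figure mixes horizons and should not be used.

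**Conclusion.** The point holds as a defect in how a secondary outcome is specified. Sections 4.4 and 4.5 name different intervals, and the chosen summary cannot accommodate women who never reach the end event. If the interval ends at ripening or oxytocin start, the plan's own rates imply about 1 against 10 women per 30 without a value at 12 hours. A mean of the available times would then compare unlike subsets and understate the difference between arms. The understatement is about 43 to 53% at 12 hours under the assumed Weibull shapes. At 15 hours it is 45% under constant hazards and falls to 20% at shape 3. These percentages are illustrative; the unequal counts follow directly from the protocol. The documents do not support saying that failures will be dropped, nor any figure for an interval ending at expulsion. The primary outcome, a proportion by 15 hours, is not affected.

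**What to change.** - Define one secondary interval in section 4.4: first application of study medication to expulsion, as already timed in section 4.5.
- Analyse it over all randomised women with the planned Kaplan-Meier method. Report the median by arm (stated as not reached if fewer than half expel by 15 hours) and the difference in restricted mean time to 15 hours with its 95% CI, in place of the plain average.
- Use the observed time for every woman who expels by 15 hours, including any who do so after being labelled a treatment failure. This keeps the secondary outcome consistent with the primary one.
- Count women who do not expel vaginally by 15 hours, including those delivered by caesarean, as not expelled through 15 hours. Do not drop them or censor them at the time of failure; censoring there would be informative.

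The cost is a few lines of text. The times are already to be recorded and Kaplan-Meier is already planned, so no new data are needed. The 15-hour horizon is the one in the primary outcome.
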